### Study design

A prospective 8-week, two-arm, single-center, single-blinded parallel-group RCT with a pretest and follow-up will be conducted by an MDT. Female patients who are diagnosed with BC and waiting to start chemotherapy or who are in the early or middle stage of chemotherapy will be randomized to receive either usual dietary care or the multidisciplinary early dietary management intervention. The participants in the intervention group will receive the multidisciplinary early intervention measures constructed based on the ITHBC. In contrast, the control group will receive only the usual cancer dietary care education at admission and education manuals based on the Dietary Guidelines for Chinese Residents, the World or American Guidelines, etc. The intervention consists of the following eight themes, with sessions provide once per week: adverse reaction coping, dietary information and habit regulation, self-care self-efficacy training, treatment self-regulation training, dietary supplement and TCM use, social support seeking, weight management, and outcome expectation education. Detailed information is provided in Fig. 1. Eight intervention sessions will be provided throughout admission for chemotherapy and a home-based interval chemotherapy period. This intervention will be initiated during the early and middle stages of chemotherapy. Standard chemotherapy cycles include 4, 6, and 8 cycles. For example, for patients receiving 4 chemotherapy cycles, the first intervention session will be provided during the first or second admission for chemotherapy. For patients receiving 6 cycles, the first intervention session will be provided during the first, second, third, or fourth admission. For patients receiving 8 cycles, the first intervention session will be provided during the first, second, third, fourth, fifth or sixth admission. The duration of intervention sessions during different chemotherapy cycles is shown in Fig. 2. In addition to the baseline measurements, follow-up measurements were taken immediately after the end of the intervention (T_1_) and at 1 (T_2_), 3 (T_3_), 6 (T_4_) and 12 months (T_5_) after the intervention. T_1_ was measured immediately after the end of the eighth intervention session. T_2_, T_3_, T_4_ and T_5_ will be measured 30, 90, 180 and 360 days after the T_1_ measurement date, respectively. The intervention process is shown in Fig. 3. The same time points for follow-up in the intervention group will be also used for the control group.

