### Implementation of the multidisciplinary early intervention

A total of 8 intervention sessions will be conducted once a week, each lasting approximately 1.5–2 h. The intervention will begin during the early or middle stage of the whole chemotherapy cycle and continue through admission and a home-based interval chemotherapy period. During the first chemotherapy admission, patients will receive face-to-face group or individual interventions. During the home-based interval chemotherapy period, online meetings, WeChat messaging, or telephone calls will be adopted. The core elements of the 8 intervention sessions are listed as follows:

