Intervention session 1 (topic: adverse reaction management): After the participants receive chemotherapy during admission and 1 day before hospital discharge, the MDT members will introduce themselves and the describe intervention process face-to-face, and patients will become familiar with each other. This session will include group interventions, group discussions and lectures: (1) patients will share their experiences with chemotherapy and diet; the group will discuss their own disease and chemotherapy experiences and diet change trajectory; (2) a nurse will show a professional video from the China Central Television (CCTV) “Health Road” program about BC, chemotherapy and diet; (3) oncologists, nurses, and dietitians will introduce the trend of common adverse reactions and the corresponding dietary self-management tips during different chemotherapy periods, including early, middle, and late-term chemotherapy or chemotherapy during admission or the interval period; and (4) oncologists will clarify the boundaries between dietary self-management and medication management when adverse reactions occur.Intervention session 2 (topic: dietary information and habit regulation): A combination of online group and individual intervention sessions will be conducted during the first week of the home-based interval chemotherapy period after session 1, which will include the following: (1) oncologists and dietitians will hold an online group Tencent conference to introduce authoritative sources of dietary information for cancer patients, such as WeChat public accounts, short videos, guidelines, and distributed information in the form of electronic materials; (2) dietitians and TCM practitioners will focus on correct dietary habits and misunderstandings for individuals with different demographic characteristics during telephone calls or WeChat messaging, including discussing the relationship between dietary intake and hormone levels for hormone receptor-positive patients, providing nutrition and weight management clinics and food therapy for patients with higher family income or abnormal weight; and (3) dietitians will demonstrate methods of dietary intake self-assessment by online video presentations, using simple and intuitive representations such as “a handful, a fist, 1 g or 2 g of quantitative salt spoons”.Intervention session 3 (topic: self-care self-efficacy training): The online group session during the second week of interval chemotherapy after session 1 will include the following: (1) nurses will guide patients to disclose their concerns about participating in their diet self-management; (2) the psychologist will lead “evidence check” and “advocate” sessions: patients will be asked to write evidence for and against their participation in dietary self-management on two post-it notes and then play the advocate, attacking the evidence against participation; and (3) nurses will provide diet option comparison cards to show patients the pros and cons of different dietary habits and encourage all patients to choose and share the reasons.Intervention session 4 (topic: treatment self-regulation training): Online group and individual sessions will be conducted during the third week of interval chemotherapy after session 1, which will include the following: (1) Through WeChat, the psychologist will send patients an assessment questionnaire linked to treatment self-regulation. According to the results, the patients will be divided into four groups: the autonomous motivation, introjected regulation, external regulation, and amotivation groups [31]. Then, the psychologist will explain definitions, content, and performance to the same online group Tencent conference; (2) the psychologist will explain the relationship between mood and diet and then use “identifying automatic thoughts” and “testing hypotheses” to determine the cognitive reasons for the lack of motivation among patients in the amotivation group in the process of participating in diet self-management and demonstrate stress relief techniques, such as deep breathing and listening to soothing music; and (3) nurses will invite patients in the autonomous motivation and introjected regulation groups to share their diet self-management experiences and the goals achieved.Intervention session 5 (topic: dietary supplement and TCM use): The next admission chemotherapy period after the session, which will include a face-to-face group lecture and discussion one day before hospital discharge, will include the following steps: (1) dietitians and TCM practitioners will use videos, charts, and paper materials to explain the concept, indications, and types of dietary nutritional supplements and replacement therapy (which can be divided into two categories: edible nutritional supplements as well as complementary and alternative therapies, such as moxibustion, massage, and aromatherapy); (2) through clinical practice and scenario simulations, using pictures or natural objects, oncologists and dietitians will guide patients in analyzing and choosing dietary supplements and replacement therapies according to their conditions; and (3) TCM practitioners will describe the content of food therapy that Chinese patients are interested in, popularize scientific knowledge and correct misunderstandings.Intervention session 6 (topic: social support seeking): Online group and individual sessions will be performed during the first week of home-based interval chemotherapy after session 5, which will include the following: (1) warm small things to share and express gratitude: nurses will encourage patients to write down the names of people who prepare their meals and living arrangements during chemotherapy through an online group Tencent conference and prepare a sentence, video or gift for them. (2) The psychologist will provide targeted dietary management tips related to emotion and psychology depending on the working status of patients via WeChat or telephone. For employed females, dietary advice will be provided to their families or colleagues before they return to work. Nonemployed individuals will be encouraged to share their thoughts and preferences regarding their diet with friends or neighbors who would like to help take care of them. (3) Nurses will encourage patients to share how others can help improve their diet during chemotherapy and how they seek help.Intervention session 7 (topic: weight management): Online group and individual sessions will be provided during the second week of the interval chemotherapy period after session 5, which includes (1) oncologists informing patients that being overweight is a risk factor and showing patients how to correctly measure their body weight via an online video, calculate their body mass index (BMI) and determine their BMI classification. (2) Dietitians will introduce the criteria and ranges of daily caloric intake for patients with different BMI classification via WeChat or telephone. For example, overweight and obese patients will be taught to read ingredient lists and recipes. Patients with a BMI below the normal range will be taught to choose foods rich in high-quality fat (such as omega 3 fatty acids and monounsaturated fatty acids) and protein [29, 30]. Repeated operations and repetitions will be used to test the effect. (3) Nurses will show patients and their caregivers how to exercise moderately and record daily calories using apps or memos.Intervention session 8 (topic: outcome expectation education): An online group session during the third week of interval chemotherapy after session 5 will include the following: (1) the psychologist will introduce the concept, content, necessity, classification and function of the outcome expectation related to dietary self-management to patients by an online group Tencent conference; (2) Nurses will encourage patients to write down their expectations for diet self-management on post-it notes and classify them into immediate or future goals; (3) The psychologist will use the “five-column chart” of alternative thinking to ask patients to share their views on the outcome expectations and determine the negative cognition of achieving the goal; (4) Through scenario and case studies, the psychologist will lead patients to analyze their own cognition on two outcome expectations of what points may be right or wrong, encourage them to create new goals and teach them how to stick to long-term dietary self-management monitoring; and (5) MDT members will summarize and share the gains and suggestions of this intervention with patients.

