
### Criteria for discontinuing or modifying allocated interventions

According to the criteria for discontinuing allocated interventions, the intervention will be discontinued when the participants ask to withdraw or when their health conditions worsen. In addition, the parts of the intervention that patients think are too intense to adhere to or to be unreasonable will be revised. During the intervention, we will also carefully record any suggestions given by patients and make adjustments after complete discussion.

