### Statistical analysis

We will use IBM SPSS Statistics 21.0 software to analyze the statistical data. Descriptive statistics, such as the number of patients with different ages, education levels, cancer stages and types of chemotherapy, as well as the percentage of patients in different groups relative to the total number of patients, will be calculated for different groups of demographic and clinical information. The mean and standard deviation will be used to compare the DMBQ total and dimensions scores, the SUPPH and FACT-B scores, and BMI. To compare the baseline balance between the two groups, two independent sample *t* tests, chi-square tests or Mann‒Whitney U tests, will be used, depending on whether the data distribution satisfies homogeneity of variance. The Shapiro‒Wilk test will be used to verify whether the scores of the two groups at different time points follow a normal distribution. If the data are balanced, repeated ANOVA will be adopted. Otherwise, we will use a generalized estimating equation (GEE) to analyze the intervention’s time, group, and interaction effects [36]. For all the above tests, *P* < 0.05 will indicate a statistically significant difference, the α level will be 0.05, and the tests will be two-sided. We will use intention-to-treat (ITT) analysis to minimize bias for sensitivity analysis [37]. The results of the last measurement of the patients who drop out of the study will be taken as the effect, which assumes that they complete the intervention, and the analysis will be reconducted with the GEE. Furthermore, missing data will be imputed with the mean values of the characteristics or with the help of multiple imputation methods if they are random and unrelated to the research elements.

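### Follow-up is dated from the eighth intervention session, so controls have no operational T1 date, early stoppers have no defined T1, and visit timing can differ between arms

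*Protocol article*

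**What the plan says.** Study design fixes the assessment clock in three statements. T1 "was measured immediately after the end of the eighth intervention session". The later visits "will be measured 30, 90, 180 and 360 days after the T_1_ measurement date, respectively". For the other arm: "The same time points for follow-up in the intervention group will be also used for the control group".

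Implementation of the multidisciplinary early intervention gives the session calendar. The frequency is weekly: "A total of 8 intervention sessions will be conducted once a week". Session 5, however, is tied to a hospital stay: "The next admission chemotherapy period after the session, which will include a face-to-face group lecture and discussion one day before hospital discharge". Session 8 then falls in the third home week after session 5.

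Control group: usual care describes education at admission and help on request. It has no numbered sessions.

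Criteria for discontinuing or modifying allocated interventions foresees early stopping: "the intervention will be discontinued when the participants ask to withdraw or when their health conditions worsen". Adherence to the intervention also foresees missed sessions. Neither section says when such a patient has her T1.

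**The concern.** All five post-baseline visits depend on one event, and that event can occur only in an intervention patient who reaches session 8. Two things follow.

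First, a data collector cannot apply the T1 rule to a control. Several substitutes are plausible, and they give different dates. In the intervention arm the T1 date also moves with each patient's chemotherapy admissions. The Background and Discussion both say that chemotherapy side effects disrupt eating. A difference in timing relative to chemotherapy could therefore appear as a difference in dietary management behaviour or quality of life, and could be mistaken for an intervention effect or hide one.

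Second, a patient who stops sessions because her health worsens, but who would still answer the questionnaire, has no T1 date. T2 to T5 are counted from T1, so they have no dates either. A control whose health worsens has no sessions to stop, so her follow-up has no such break. Outcome data could therefore be lost for health-related reasons in one arm only.

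**Working it through.** The plan gives offsets between visits but no day count from the start of the intervention, so there is no figure to reproduce. The check is calendar arithmetic.

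**Inputs from the protocol article**
- Eight weekly sessions; session 5 at the next admission; session 8 in the third home week after session 5 (Implementation).
- T2 to T5 at T1 + 30, 90, 180 and 360 days (Study design).

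**Assumption:** the admission that carries session 5 is late by d = 0, 7, 14 or 21 days. The documents give no delay sizes.

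**Formulae**, with session 1 as day 0:
- Session k without delay falls on day 7 × (k − 1), so session 5 is on day 28 and session 8 on day 49.
- T1 = 49 + d; each later visit = T1 + offset.

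| Delay d (days) | T1 | T2 | T3 | T4 | T5 |
|---|---|---|---|---|---|
| 0 | 49 | 79 | 139 | 229 | 409 |
| 7 | 56 | 86 | 146 | 236 | 416 |
| 14 | 63 | 93 | 153 | 243 | 423 |
| 21 | 70 | 100 | 160 | 250 | 430 |

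**Shift as a share of the undelayed time to each visit**
- T1: 7/49 = 14% to 21/49 = 43%.
- T2: 7/79 = 9% to 21/79 = 27%.
- T5: 7/409 = 1.7% to 21/409 = 5.1%.

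The shift in days is the same at every visit, but its relative weight is concentrated at T1 and T2.

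**Difference between arms** (intervention T1 minus control T1), by how a control's T1 is dated:
- Control T1 on day 49 (seven weekly gaps): 0, 7, 14 or 21 days.
- Control T1 on day 56 (reading the trial as 8 full weeks): −7, 0, 7 or 14 days.
- Control T1 matched to the intervention calendar: about 0.

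The text permits all three and does not choose. Even with no delay, the first two differ by 7 days.

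**Early stoppers.** Setting the sections side by side: T1 requires the end of session 8 (Study design), the intervention may stop before session 8 (Criteria for discontinuing), and T2 to T5 require the T1 date (Study design). For a patient who stops at, say, session 4, no stated rule yields any post-baseline visit date. The number of such patients cannot be derived from the documents.

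**The case against.** **Controls are covered.** A reader might infer that controls have no follow-up schedule at all. The documents do not support that: Study design gives them the same time points, and the weekly sessions and 8-week length suggest a nominal T1. An article may also leave visit windows to the full protocol, and Figs. 2 and 3, which might settle the calendar, are not shown. This stands as a limit on the point. It does not remove it, because the article states a T1 rule and that rule cannot be applied to a control.

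**A difference in timing is not demonstrated.** Correct. Chemotherapy delays occur in both arms, and matched timing would bring the difference close to zero. The text permits a difference but does not establish one.

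**Stopping sessions is not leaving the study.** A reader might infer that early stoppers are analysed at their baseline value, or might use the 20% loss in Sample size to count them. Neither is supported. Carry-forward is written for those who leave the study ("The results of the last measurement of the patients who drop out of the study will be taken as the effect") and belongs to a sensitivity analysis, and the same section also names multiple imputation. The 20% is loss to follow-up at any time, not the rate of stopping sessions while still assessable. It could also be argued that T1 means the end of whatever intervention the patient received, since Study design and the Fig. 3 caption also describe T1 as immediately after the intervention. That reading would give early stoppers a T1, but at a different time from everyone else, and the more specific sentence names the eighth session.

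**A fixed calendar has its own cost.** Session 8 falls at a consistent point after an admission, and a clock from the bare randomisation date would lose this. Some patients are randomised while still waiting for chemotherapy. With an assumed wait of 21 days, day 56 from randomisation is day 56 − 21 = 35 after session 1, which is the day of session 6. This stands, and it rules out the bare randomisation date as the origin. It does not defend the present rule, which secures that consistent point for intervention patients and states nothing equivalent for controls.

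**Conclusion.** The point holds in a limited form. The stated rule gives controls a nominal schedule without an operational T1 date. It lets T1 move with the session 5 admission in the intervention arm, and it leaves T1 to T5 undefined for patients who stop sessions early but could still be assessed.

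Under assumed delays of 7 to 21 days and a control T1 fixed at day 49, the arms differ by 7 to 21 days. That matters mainly at T1 and T2 and is minor by T5. The effect on questionnaire scores cannot be calculated, because the documents do not say how fast the scores change with time since chemotherapy. The loss of data from early stoppers is a possibility that the rule creates, and its size is unknown. The change should be made because it is cheap and protects the primary outcome. The documents do not show that the comparison is already biased.

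**What to change.** Date T1 to T5 in both arms from one origin that exists for every patient and is set in the same way in each arm. T0 or the first chemotherapy admission after randomisation would serve. If T0 is used, it should not fall during a wait for chemotherapy, or it shares the weakness of the randomisation date. Set T1 at a fixed interval of about 8 weeks, T2 to T5 at 30, 90, 180 and 360 days after the scheduled T1 (not the actual T1), and one visit window for both arms. State that every randomised patient is assessed on this calendar, whatever the number of sessions attended and whether or not the intervention was discontinued.

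The cost is a few sentences in the protocol and analysis plan, with no extra visits and no change to care. The downside is that some intervention patients with late admissions will have T1 before session 8. If the origin coincides with session 1 and T1 is on day 56, a 7-day delay puts session 8 on the T1 date, and delays of 14 and 21 days put T1 earlier than session 8 by 63 − 56 = 7 and 70 − 56 = 14 days. Recording the date of session 8 and the date of the last chemotherapy admission at each visit would let the analysis describe this.

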
**Fig. 1 Fig1:**
[figure not shown]
Conceptual frameworks for the multidisciplinary early intervention. BMI: body mass index; DMBQ: Dietary Management Behavior Questionnaire for breast cancer patients treated with chemotherapy; ITHBC: Integrated Theory of Health Behavior Change; TCM: traditional Chinese medicine

**Fig. 2 Fig2:**
[figure not shown]
Initiation of the multidisciplinary early intervention for patients with different numbers of chemotherapy cycles. AC: each admission chemotherapy ×: possible time to start the intervention (early and intermediate stages of the whole chemotherapy cycle); a blank space: a one-week intermission of chemotherapy at home

**Fig. 3 Fig3:**
[figure not shown]
The flow chart of the intervention process in this RCT. T_0_: before the intervention; T_1_: immediately after the intervention; T_2_: 1 month after the intervention; T_3_: 3 months after the intervention; T_4_: 6 months after the intervention; T_5_: 12 months after the intervention. BMI: body mass index. RCT: randomized controlled trial

